### Sample size determination

The sample size for this study was determined using the formula for comparing two proportions [41]. The primary outcome is oral hygiene status. The prevalence (P_1_ = 38.4%) of children who had good oral hygiene from a previous study in Nigeria [42], was used for sample size calculation. An estimated 50% increase in the proportion of participants with good oral hygiene following the intervention (P_2_ = 57.6%) was used in calculating the minimum sample size. Other considerations were statistical power of 80%, a significance level of 5%, a non-response rate of 10%, an attrition rate of 20%, and an estimated design effect of 1.5. A minimum of 212 participants will be recruited per study group, making 424 for the two groups.

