### Baseline data collection

Interviewer-administered semi-structured questionnaire (S2 File) will be used for data collection. The questionnaire will be developed from the review of related local literature [12, 42, 45], and will be pretested and validated for use among the study participants. The oral examinations will be based on the WHO Oral Health Surveys: Basic Methods, 5^th^ Edition [46]. Five trained and calibrated dentists will conduct the interview and oral examinations. The dentists will be trained by an expert in oral epidemiology using the WHO guideline [46]. The questionnaire will be used to collect information on the participants’ sociodemographic characteristics, oral hygiene knowledge, attitude, and practices. While the children will be the main respondents, their parents (preferably mothers) will be called by the research assistants to validate the information provided by the children regarding the sociodemographics and oral hygiene behaviour. The oral examination will assess the participants’ oral hygiene status (simplified oral hygiene index [47]) and their lifetime caries experience [sum of decayed, missing, and filled teeth (dmft/DMFT) [46, 48]]. Based on the simplified oral hygiene index (OHI-S), indexed teeth would be assessed. On the upper jaw/maxilla, the Right and Left First Molar (UR6, UL6) and Right Incisor (UR1) will be assessed. Similarly, both the Right and Left First Mandibular Molars (LR6, LL6) and the Left Mandibular First Incisor (LL1) will be examined in the low jaw/mandible [47]. If any of these teeth are absent, another designated tooth in the segment will be examined [47]. The oral examination will be done using a sterile wooden mouth spatula, probes, and dental mirrors. The oral examination will be conducted near the windows in the school halls, with the participants seated upright facing the window such that the examination is aided by good illumination from natural light. Baseline data collection will be conducted in both study groups (test and control) one week before delivering the interventions.

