### Post-intervention data collection

There will be three sessions of post-intervention assessments—Immediate, six, and 12 months. The immediate post-intervention assessment will collect information on the participants’ oral hygiene knowledge and attitude immediately after the second session of the intervention is completed. The 6-month post-intervention assessment will be conducted six months after the immediate post-intervention assessment. Information on the participants’ oral hygiene knowledge, attitude, and practices will be collected. Oral examinations will also be done to assess the participants’ oral hygiene status using the simplified oral hygiene index. The 12-month post-intervention assessment will be conducted 12 months after the immediate post-intervention assessment. It will involve oral health examinations to check the participants’ oral hygiene status and dental caries experience (dmft/DMFT), along with assessing the participants’ oral hygiene knowledge, attitude, and practices. The same questionnaire for the pre-intervention assessment will also be used for the post-intervention assessments. However, the immediate post-intervention assessment will not include oral examinations. The questionnaires for 6 and 12 months post-intervention data collection will include a question to assess if the participants have been taught oral hygiene practices (through songs or lectures) by pupils from other schools during the study period. This is to get data on the potential contamination and control for this during the data analysis (sub-analysis).

Figs 2 and 3 show the SPIRIT schedule and Flow diagram for the study, respectively.

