#### Data analysis plan

Baseline data would be compared among the two study groups based on their sociodemographic characteristics and the baseline value of the outcome variables (oral hygiene status, DMFT/dmft, caries status, knowledge, attitude, and practice). Subsequently, the intervention effects on the outcome variables will be assessed over the study period (baseline, immediate, 6 months, and 12 months assessments). The effectiveness would also be compared between groups (test vs control) over the 12 months (baseline, 6 months, and 12-month assessment). An intention-to-treat analysis will be employed for this study [51]. A participant will remain in the originally assigned group, notwithstanding what happens during the study, such as deviation from the study protocol or loss to follow-up. The data obtained at the previous assessment will be recorded for those lost to follow up in the subsequent assessments. The level of statistical significance for all tests will be set at p < 0.05.

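### Carry-forward as the only missing-data rule gives every child missing at 12 months a pre-intervention caries value and every child lost before 6 months a pre-intervention OHI-S

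*Protocol article*

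**What the plan says.** The Data analysis plan states "An intention-to-treat analysis will be employed for this study", keeps each child in the assigned group, and then sets the rule for missing outcomes: "The data obtained at the previous assessment will be recorded for those lost to follow up in the subsequent assessments". It names no outcome as exempt, and gives no missing-data assumption, alternative method or sensitivity analysis.

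The examination schedule decides which value is carried:

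- **Baseline** (Baseline data collection): OHI-S and dmft/DMFT, taken "one week before delivering the interventions".
- **Immediate** (Post-intervention data collection): "the immediate post-intervention assessment will not include oral examinations".
- **6 months** (same section): "Oral examinations will also be done to assess the participants’ oral hygiene status using the simplified oral hygiene index". Caries is not listed.
- **12 months** (same section): OHI-S and dmft/DMFT.

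The primary outcome section names three measures: caries experience, current caries status and oral hygiene status. The sample size rests on oral hygiene status and allows for "an attrition rate of 20%, and an estimated design effect of 1.5".

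**The concern.** Intention-to-treat fixes the group in which a child is analysed. It does not require an outcome to be supplied for a child who was not examined. Here the supplied value is the last one on file, and the schedule often makes that a value from before the intervention.

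- **Caries.** With no examination between baseline and 12 months, a child missing at 12 months always receives the baseline value. Change is set to zero for that child on two of the three primary measures. The Discussion itself treats dmft/DMFT as an index that does not go down and expects changes in tooth condition to be noted at 12 months. Carry-forward rules out any such change for a child who is lost.
- **OHI-S.** A child lost before the 6-month examination receives the baseline value at both 6 and 12 months. A child lost after it receives a 6-month value, which is post-intervention but half a year old.

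At 20% attrition, about 42 of 212 children per arm (0.2 × 212 = 42.4) would have a filled 12-month value counted as observed. The estimated effect may be shifted, and its standard error will be smaller than the examined children support.

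**Working it through.** **Inputs from the protocol** (Sample size determination): P1 = 0.384, P2 = 0.576, power 80%, significance level 5%, non-response 10%, attrition 20%, design effect 1.5, 212 per group. **Assumptions**, because the protocol is silent: two-sided test; baseline 38.4% in both arms; control stays at 38.4% and test reaches 57.6%; loss unrelated to outcome; 6-month effect equal to 12-month effect unless stated.

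**1. The plan's own sample size.** Unpooled two-proportion formula: (1.96 + 0.8416)² × (0.384 × 0.616 + 0.576 × 0.424) / 0.192² = 7.849 × 0.4808 / 0.03686 = 102.4. Then 102.4 × 1.5 / (0.9 × 0.8) = 213.3, against 212 stated. The figure reproduces within 1%, so nothing below rests on a sample-size error.

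**2. Equal loss, OHI-S.** Let s be the share of the 20% lost before the 6-month examination. The expected test proportion is 0.576 − 0.2 × s × 0.192, and control stays at 0.384. Power uses 212 × 0.9 = 190.8 children per arm, 190.8 / 1.5 = 127.2 effective, and Φ(difference / SE − 1.96).

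| Share lost early | Difference | SE | Nominal power |
|---|---|---|---|
| 100% | 0.5376 − 0.384 = 15.4 points | 0.0618 | 0.70 |
| 50% | 0.5568 − 0.384 = 17.3 points | 0.0616 | 0.80 |
| 0% | 0.576 − 0.384 = 19.2 points | 0.0615 | 0.88 |

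With all 212 per arm analysed (no non-response deducted), the powers are about 0.74, 0.83 and 0.90, using the pooled-variance form of the test.

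For comparison, take examined children only: 212 × 0.9 × 0.8 = 152.6 per arm, 101.8 effective, SE 0.0687, expected difference 19.2 points, power 0.80. Carry-forward therefore has less power than the examined children alone once more than half the losses are early. Its apparent gain when losses are late comes from counting filled values as observed.

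**3. Fading effect.** Illustrative assumption: 19.2 points at 6 months, 10 points at 12 months, 20% equal loss, all after 6 months. The carried-forward contrast is 0.8 × 10 + 0.2 × 19.2 = 11.8 points against a true 10.

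**4. Unequal early loss, no true difference.** Assume both arms rise from 38.4% to 57.6%. The false difference is (difference in loss) × 19.2 points:

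- 18% vs 22%: 0.04 × 19.2 = 0.8 points
- 15% vs 25%: 0.10 × 19.2 = 1.9 points
- 10% vs 30%: 0.20 × 19.2 = 3.8 points

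It favours the arm that lost fewer children, so it can go either way. In a simulation of 40,000 runs at 141 effective children per arm (212 / 1.5), the 10% vs 30% case gave a type I error of about 9.6%.

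**5. Caries.** If lost and retained children would have had the same mean increment, carry-forward shrinks an arm's mean change by its loss fraction. With equal true increments of 0.3 to 0.5 teeth (assumed) and 30% vs 10% loss, the false difference is 0.2 × 0.3 = 0.06 to 0.2 × 0.5 = 0.10 teeth, in favour of the arm that lost more.

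**6. Precision.** Counting 212 rather than 0.8 × 212 = 169.6 children as observed multiplies the standard error by √0.8 = 0.89. In the simulation with 20% equal early loss and a true 19.2 points, carry-forward gave SE 0.058 and 95% interval coverage of about 0.905. Examined children alone gave 0.065 and 0.948.

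**The case against.** The best defence is that the harm depends on when and where children are lost, and the protocol gives no reason to expect a bad pattern. Both arms have three sessions of matching length, and the class was chosen partly because its pupils tend to stay in school. If loss is equal and the arms do not truly differ, the mean contrast is unbiased. If half the losses come after the 6-month examination, nominal power is back at 0.80. All this stands, and it is why the size is given as a range. Loss of 10% vs 30% is an illustration, and nothing in the document predicts it.

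Four stronger readings are tempting and are not supported:

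- **That every lost child receives a pre-intervention OHI-S.** The 6-month examination prevents this for later losses. For caries, the statement does hold for every child missing at 12 months.
- **That power falls to 0.70.** This requires all 20% to be lost before 6 months.
- **That the rule always errs toward no effect.** Steps 3 and 4 show otherwise.
- **That the 20% attrition allowance contradicts the rule.** Inflating the sample for loss is cautious and compatible with any later missing-data method.

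Two further limits apply. The coverage shortfall in step 6 comes mostly from the shifted estimate, so understated uncertainty is the lesser harm. The protocol also plans group means and prevalence for caries rather than increments, so the shrinkage in step 5 applies to change from baseline under equal increments in lost and retained children.

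The defence does not rescue the rule. It is stated outright rather than left to an analysis plan, and no assumption is offered to justify it.

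**Conclusion.** The rule is wrong as written. It is firmest for caries, where by the text every child missing at 12 months is given a pre-intervention value. For OHI-S the same applies to children lost before the 6-month examination, while later losses carry a 6-month value.

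Under the protocol's proportions, equal 20% loss and a stable effect, the expected difference lies between 15.4 and 19.2 points, with nominal power from about 0.70 to 0.88 at 191 per arm and design effect 1.5. Unequal early loss with improvement in both arms adds a false difference of 0.8 to 3.8 points over the imbalances tried, in either direction. A fading effect can be overstated. Standard errors are too small by a factor of about 0.89 relative to the children examined.

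Timing of loss, imbalance, fading and caries increments are all assumptions. The reading that caries is not examined at 6 months rests on the text, because the schedule figure is not available.

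**What to change.** - Delete the carry-forward sentence. Leave missed assessments missing in the data set, and keep every child in the allocated group.
- Analyse all observed baseline, 6-month and 12-month values with a likelihood-based mixed model suited to each outcome type, with school as a random effect and a small-sample correction for eight schools. Without that correction, the replacement could itself understate the standard error. Multiple imputation that includes arm, school, baseline and 6-month values is an alternative.
- Add one missing-not-at-random sensitivity analysis that states the assumption made for lost children in each arm.
- Keep carry-forward, if at all, as a labelled sensitivity analysis.

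The cost is a change of wording in the analysis plan and slightly more analysis work. No extra data are needed, and the sample size is unaffected.

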### Ethical considerations

The study has been registered with the Pan African Clinical Trial Registry (PACTR202010863892797). Ethical approval was obtained from the University of Ibadan/University College Hospital Ethical Review Committee (Registration number: NHREC/05/01/2008a). The permission to carry out the study was also received from the Ministry of Education, Oyo State. The following ethical issues will be considered:

#### Written informed consent

A letter to the parents or legal guardians will request their consent for their children or ward to participate in the study. An information sheet stating the details of the study will be given to them to read, after which they will be asked if they understood what the study is about and what is expected of their children/wards. Parents/legal guardians who agree to allow their children/wards to participate in the study will be asked to sign a written Informed Consent form, and their children will subsequently sign the assent form.

#### Confidentiality of data

All information collected from respondents during this research will be kept confidential. All identifiable details of the participants will be separated from the coded details and collected data. The identifiable details and data entered on the computer will be password-protected and only accessible to the researchers and data entry clerks.

#### Right to withdraw from the study

Study participants who wish to withdraw from the study will be allowed to do so freely at any point in time and without any negative repercussions.

#### Beneficence/Non-maleficence

The study participants will benefit from the educational intervention during or immediately after the study, and the study does not pose any harm to the participants.

#### Dissemination

Findings from the study will be presented at both local and international conferences and published in peer-reviewed journals.

## Discussion

A multi-disciplinary team comprising community dentists, paediatric dentists, restorative dentists, and music experts was established to develop a traditional rhyme (Folk Song) to be used as a tool for oral hygiene promotion among children in two rural communities in Nigeria. The team, together with children, teachers, and parents, co-developed a simple, memorable, and age-appropriate traditional song [49] as the platform for delivering oral hygiene behavioural change to children to enhance their self-efficacy with twice-daily tooth brushing.

To the best of our knowledge, this is one of the few studies to assess the effectiveness of traditional folk songs in improving children’s oral hygiene knowledge, attitude, and practices. Folk songs are very popular in Nigeria, and it is not just for entertainment but also to convey historical events and heritage and teach children about important virtues [52, 53]. This study aims to use folk songs to deliver oral health education to children in two rural communities—Igboora and Idere, Oyo State, Nigeria. The burden of oral health problems is high in Nigeria, like other African countries, and those in rural areas are more affected [13]. This is one of the reasons these communities were selected for the intervention. Like other rural communities in Nigeria, access to oral health services is also limited in these communities. However, the Department of Periodontology and Community Dentistry, University College Hospital/University of Ibadan, provides basic oral health care services to these communities through the Primary Oral Health Care clinics, and some of the investigators of this research are in charge of the clinics. This relationship would facilitate a quick uptake of outcomes of this research in the subsequent planning of intervention programmes from the dental clinics in responding to oral health challenges in the study sites.

Pupils in primary schools have been targeted for this intervention because the school provides an organised setting where the participants can be taught without distractions. It also gives the best opportunity for the participants to be followed up with a lesser risk of attrition. The intervention can also be easily sustained by incorporating it into their activities during the daily morning assembly.

A school/cluster-level randomisation will be employed to avoid having participants in the intervention and control groups in the same school, which may increase the risk of spillover [54]. There is no way some participants in a school would be taught these songs, and others in the control group would not be aware if they were in the same school. In the same vein, the distance of schools will be considered when selecting the schools for the study and schools close to each other would not be allowed to be in different study groups.

This study will consider several outcomes, including knowledge, attitude, practice, and oral health status (caries and oral hygiene). This would generate empirical information on the effectiveness of folk songs on each of these outcomes separately. A possible limitation in the outcome measurement is the dmft/DMFT.

The dmft/DMFT is a non-reversible index [48]; thus, the score at baseline would not reduce at the study completion even if the participant has treated carious teeth. To address this, the condition of the teeth (decayed, missing, and filled) would be noted at baseline. Hence, if a participant visited the dental clinic to fill a decayed tooth, such would be noted as an improvement in the caries experience during the final assessment 12 months post-intervention.

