### Variables

#### Primary outcome variables

The participants’ oral health status will be the primary outcome variable. There would be three measures, including the caries experience, which would be based on the oral examination of the dmft/DMFT scores, current caries status [48], and oral hygiene status [47].

The DMFT/dmft will be calculated for each participant by summing up all the carious, filled, and missing teeth due to caries in their mouth. Subsequently, the mean DMFT and mean dmft will be calculated by dividing the sum of the DMFT/dmft scores for each group by the total number of participants in the group and reported separately for the two study groups. The caries prevalence would also be assessed by dividing the number of participants with at least one carious tooth over the total number of participants in each group.

The oral hygiene status will be assessed using the simplified Oral Hygiene Index (OHI-S) [47]. The maximum score for OHI-S is six. Based on their score, each participant will be assigned these three categories: “Good” (0.0–1.2), “Fair” (1.3–3.0), and “Poor” (3.1–6.0) [47].

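### The Discussion counts a filled tooth as an improvement in caries experience, but the protocol's own definition of that measure leaves it unchanged

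*Protocol article*

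**What the plan says.** The Primary outcome variables section names three measures of oral health status. Two of them concern caries: "the caries experience, which would be based on the oral examination of the dmft/DMFT scores, current caries status". The third is oral hygiene status. The score for each child is obtained by "summing up all the carious, filled, and missing teeth due to caries in their mouth", and group means are then reported for DMFT and dmft. Baseline data collection uses the same definition: "lifetime caries experience [sum of decayed, missing, and filled teeth (dmft/DMFT".

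The outcome section also defines caries prevalence, which counts only untreated decay: "dividing the number of participants with at least one carious tooth over the total number of participants in each group". This appears to be the summary of current caries status.

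The Discussion takes up the index as a possible limitation. It accepts that "the score at baseline would not reduce at the study completion even if the participant has treated carious teeth". As the remedy, it says that "the condition of the teeth (decayed, missing, and filled) would be noted at baseline", and concludes that "if a participant visited the dental clinic to fill a decayed tooth, such would be noted as an improvement in the caries experience" at the final assessment, 12 months after the intervention.

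**The concern.** The Discussion attaches the improvement to caries experience, the same term that the Methods define as a cumulative sum. A sum that includes filled teeth cannot improve because a decayed tooth was filled. The 12-month result for a primary measure therefore has two incompatible readings, and an analyst could follow either.

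The choice affects what the arms are compared on. Under the Methods definition, a difference in caries experience reflects new disease. Under the Discussion statement, part of the difference can come from who had decayed teeth treated. According to the Intervention and control groups section, the song covers brushing frequency, toothpaste, the tongue and brushing technique; dental visits are not among the messages listed. Treatment uptake would then enter the estimate of a preventive effect by a route that the intervention is not described as acting on.

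**Working it through.** The point is one of definition, and the plan gives no figure of its own for it. The check is to score the same tooth histories under each section.

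**Inputs.** The dmft/DMFT sum is D + M + F (decayed, missing due to caries, filled), from Primary outcome variables and Baseline data collection. Caries prevalence means D of at least 1, from Primary outcome variables. The filling statement comes from the Discussion.

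| Change from baseline to 12 months | D + M + F | At least one carious tooth | Discussion statement |
|---|---|---|---|
| Two decayed teeth, one filled | 2+0+0 = 2, then 1+0+1 = 2 | yes, then yes | improved |
| One decayed tooth, filled | 1+0+0 = 1, then 0+0+1 = 1 | yes, then no | improved |

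The defined score is unchanged in both rows, while the Discussion records an improvement in both. Caries prevalence picks up the filling only in the second row, where the last carious tooth has been treated.

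**What crediting fillings could do.** None of the following figures is in the protocol. Assume that each filling is credited as one tooth, that children in both arms start with a mean of 1.0 decayed tooth, and that both arms gain 0.2 newly affected teeth per child over 12 months. Let 5% of decayed teeth be filled in one arm and a share *f* in the other.

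- Change in the defined score: +0.2 in each arm, so the difference is 0 whatever *f* is.
- Change in a score that credits fillings: 0.2 − 1.0 × share filled. The first arm gives 0.2 − 0.05 = 0.15.
- With *f* = 5%: 0.15 in the other arm, a difference of 0.
- With *f* = 15%: 0.2 − 0.15 = 0.05, a difference of 0.05 − 0.15 = −0.10 teeth per child.
- With *f* = 30%: 0.2 − 0.30 = −0.10, a difference of −0.10 − 0.15 = −0.25 teeth per child.

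New disease is identical in both arms, so every non-zero difference here comes from treatment alone. If the two arms' filling shares are exchanged, the sign reverses. The example shows the mechanism; it does not estimate what this trial would see.

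**The case against.** The best defence is that the Discussion sentence does not change the score at all. It says that a filling will be *noted*, it gives no scoring formula, and it has just said that the score does not fall after treatment. On this reading it describes keeping the D, M and F components separately, under a loose label, and the change properly belongs to current caries status. Recording the components is sound practice.

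Part of this stands. A reader might infer that each filling lowers a child's dmft/DMFT by one; the protocol does not say so. But the sentence is offered as the cure for a limitation of outcome measurement, it names the 12-month assessment, and it places the improvement under caries experience even though the outcome section lists current caries status separately. This is a statement in conflict with the definition, not a detail left to an analysis plan.

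Other inferences go further than the protocol allows:

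- *That the outcome would simply measure dental attendance.* New decay would still raise the sum, so the result would be a mixture.
- *That the investigators' role in the local clinics biases the comparison.* The Discussion mentions that role in connection with uptake of the findings, and nothing shows that clinic access differs by arm. The control arm receives dentist-led sessions, so any effect on attendance could favour either arm.
- *That shedding of primary teeth produces a false treatment effect.* Since missing teeth count only when lost to caries, a decayed primary tooth shed naturally drops out of dmft. This would be expected in both arms and is mainly noise. DMFT and dmft means are also calculated separately.

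**Conclusion.** The contradiction is real and should be resolved before the 12-month data are scored. Two Methods sections define caries experience so that filling a decayed tooth leaves it unchanged; the Discussion calls the same event an improvement in it. Followed as written, the Discussion statement would count treatment uptake as benefit on a primary measure.

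The size and direction of any distortion in this trial are unknown, because they depend on a crediting rule and on filling rates by arm that the protocol does not give. The conclusion needs only the definitions and no assumed figure. It does not touch the oral hygiene comparison or the sample size of 212 per group, which was calculated from proportions with good oral hygiene (38.4% and 57.6%).

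**What to change.** Delete the statement in the Discussion that a filling counts as an improvement. State that caries experience at 12 months is scored only as in Primary outcome variables. Keep the component records and report decayed-to-filled changes by arm, labelled as treatment uptake. Such changes register under current caries status only when a child's last carious tooth is filled, so the separate count adds information. This is a change of wording and alters no primary measure.

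As an option, add a supportive analysis: the number of teeth newly decayed, filled or missing due to caries between baseline and 12 months. Report it separately for permanent and primary teeth, because dmft can also fall through natural shedding. Tooth condition is already to be noted at baseline and dmft/DMFT is already examined at 12 months, but both charts would have to be kept tooth by tooth, which must be settled before baseline. Some primary teeth shed between the two visits could not be classified, which is a reason to keep this analysis supportive and not let it replace the defined measure.

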The participants in the control group will be exposed to conventional health education on adequate oral hygiene practices conducted by the dentist [50]. Similar to the test group, there will be three intervention sessions. The first session will last for 40 minutes and will involve expert-led health talks and question and answer with the participants. The second and third sessions will also take place after two and four weeks, respectively. The follow-up sessions will involve revising the oral health messages with the participants, lasting for about 20 minutes each. None of the participants (control and test groups) will be denied access to oral health talks that they may be exposed to away from school.

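### The Discussion would note a filled tooth as an improvement in caries experience, although the protocol's own DMFT/dmft definition leaves that measure unchanged by a filling

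*Protocol article*

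**What the plan says.** Under *Primary outcome variables*, oral health status has three measures: caries experience, current caries status and oral hygiene status. The first is described as "the caries experience, which would be based on the oral examination of the dmft/DMFT scores", and each child's score is obtained by "summing up all the carious, filled, and missing teeth due to caries in their mouth". *Baseline data collection* describes the same quantity as "their lifetime caries experience [sum of decayed, missing, and filled teeth (dmft/DMFT", that is, as a cumulative measure. Caries prevalence is defined separately, by "dividing the number of participants with at least one carious tooth over the total number of participants in each group".

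The last paragraph of the *Discussion* treats the index as a possible limitation because it is not reversible: "the score at baseline would not reduce at the study completion even if the participant has treated carious teeth". As the remedy, it proposes to note whether teeth are decayed, missing or filled at baseline. It then adds that "if a participant visited the dental clinic to fill a decayed tooth, such would be noted as an improvement in the caries experience" at the final 12-month assessment. Nothing elsewhere in the article overrides or qualifies that sentence.

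**The concern.** The same event on the same named outcome has two readings. Under the outcome definition, a filling is no change in caries experience. Under the *Discussion*, it is an improvement in caries experience.

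The second reading does not suit this measure. A filling shows that the tooth had already decayed and that the child then obtained care; it does not show less disease. If children are classified or described as improved on this basis, the 12-month account of a primary measure mixes dental treatment with caries.

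Attendance could differ between arms, in either direction. Control pupils receive "conventional health education on adequate oral hygiene practices conducted by the dentist", whereas test pupils learn the song from a researcher and sing it under a teacher's supervision. Contact with a dentist could prompt more clinic visits in the control arm, which under this sentence would favour control. Local care comes through clinics where "some of the investigators of this research are in charge of the clinics"; these serve both communities, and nothing ties them to one arm. If fillings rose equally in both arms, each would still show an apparent gain over time in caries experience that its own formula does not register.

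**Working it through.** **The plan's own figure.** The only sizing calculation rests on oral hygiene status. With the stated P1 = 0.384, P2 = 0.576, 80% power and 5% significance (taken as two-sided), the unpooled two-proportion formula gives

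n = (1.960 + 0.842)² × [0.384 × 0.616 + 0.576 × 0.424] / 0.192² = 102.4 per group.

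Multiplying by the design effect of 1.5 and dividing by 0.9 (non-response) and 0.8 (attrition) gives 213.3, against 212 stated. No caries quantity enters, so the sample size does not depend on this point.

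**The effect of a filling on caries experience.** The definition gives DMFT = D + M + F, each tooth counting once. A filling makes D fall by 1 and F rise by 1, so the change in DMFT is −1 + 1 = 0. The same holds for dmft.

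**Three illustrative children**, with all teeth in one dentition and M = 0 throughout:

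| Child | Baseline | 12 months | DMFT | At least one carious tooth | *Discussion* sentence |
|---|---|---|---|---|---|
| A: one of two decayed teeth filled | D=2, F=0 | D=1, F=1 | 2 to 2 (change 0) | yes to yes | improved |
| B: only decayed tooth filled, one new carious tooth | D=1, F=0 | D=1, F=1 | 1 to 2 (worse by 1) | yes to yes | improved |
| C: only decayed tooth filled, nothing new | D=1, F=0 | D=0, F=1 | 1 to 1 (change 0) | yes to no | improved |

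In none of the three does caries experience fall. Child B is the clearest conflict: caries experience has worsened, current caries is unchanged, and the sentence still records an improvement. Child C does improve, but on current caries, which the protocol already measures separately.

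**What cannot be computed.** The article gives no baseline caries prevalence, no rate of new caries and no rate of fillings in either arm. It also gives no rule that turns the note into a score. The effect on a between-arm comparison therefore cannot be sized from the document.

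**The case against.** The strongest reply is that the *Discussion* says *noted*, not scored. It agrees with the outcome definition that the index will not fall, and may only be adding an observation about components beside it. The summaries that are actually specified are mean DMFT, mean dmft and caries prevalence, and *Data analysis plan* lists DMFT/dmft and caries status. None is altered by the note. All of this stands, and it limits the point. It does not remove it: the sentence is offered as the remedy for a score that does not fall, it names the primary measure, and it is tied to the final assessment.

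A reader might infer more, in four ways that the document does not support:

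- *That fillings will be subtracted from DMFT/dmft, or that a planned test has an inflated false-positive rate.* No such scoring and no binary improved endpoint is defined. Any error rate would rest on assumed treatment rates and an invented endpoint.
- *That the rule favours the song.* The one arm-specific mechanism visible in the text, a dentist delivering the control sessions, would work the other way. The *Discussion* also says access to oral health services in these communities is limited, so fillings may be few.
- *That the song cannot affect care-seeking.* The messages listed under *Intervention and control groups* concern brushing, but the list is not presented as complete and the lyrics are not shown. The Introduction names regular dental visits among common preventive measures.
- *That the prevalence measure is also faulty.* A filled tooth is properly no longer currently carious, so a fall in that measure after a filling is legitimate.

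**Conclusion.** The point holds as a contradiction in the wording of a primary measure. Caries experience is defined so that a filling changes it by exactly zero, while the *Discussion* would note the same filling as an improvement in it. Following that sentence would report treatment received as a gain in caries experience, even for a child whose DMFT has risen from 1 to 2.

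The contradiction follows from the definition alone and needs no assumed rates. Any distortion of the comparison between arms would require filling rates to differ between them; neither its direction nor its size can be established from the document. The specified means and prevalence, the oral hygiene measure and the sample size are unaffected. The sentence should be corrected before 12-month caries data are classified.

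**What to change.** 1. Delete the wording in the *Discussion* that treats a filling as an improvement in caries experience.
2. Keep the scoring under *Primary outcome variables*, and state that a change from decayed to filled is no change in DMFT/dmft.
3. Tabulate decayed-to-filled changes by arm as treatment received: a descriptive item, not a benefit.
4. If a 12-month caries increment is reported from the tooth-level data, count teeth that were sound or unerupted at baseline and are decayed, filled or missing due to caries at 12 months. This is optional and not needed to remove the contradiction.
5. Leave the current-caries prevalence measure as it is.

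The cost is a change of wording. Tooth condition is already to be noted at baseline and dmft/DMFT is already examined at 12 months, so no visit, examination or sample-size change follows. The one thing given up is describing a treated child as improved in caries experience; where no carious tooth remains, current caries status already shows it.
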